#### 2.3.4. Representational Similarity Analysis

Representational Similarity Analysis (RSA) has been effectively applied in prior studies to decode different linguistic feature representations, such as decoding multidimensional phonological representations and feature integration in language processing [77,78,79]. To investigate how different speech features (tone, vowel, consonant) are neurally represented and whether individuals with ASD exhibit altered feature integration, we perform RSA based on ERP data. Integration Complexity Models are constructed to quantify the dissimilarity stimuli (see Figure 3). Each model operationalizes dissimilarity between stimulus pairs as a function of changes in three phonological features: Tone, Vowel, and Consonant. The models differ in their weighting schemes to emphasize specific features, reflecting theoretical assumptions about their relative perceptual or cognitive salience. Below is a detailed description of each model:

##### Step 1: Constructing Theoretical RDM Models

Base Feature-Count Model

This baseline model assumes equal perceptual salience across all three features. Dissimilarity between two stimuli is defined as the sum of the number of altered features. Specifically: Tone, Vowel, or Consonant change contributes a unit weight of 1. For example, a stimulus pair differing in both Tone and Vowel (e.g., /da1/ vs. /du4/) receives a dissimilarity value of 2, while a pair differing in all three features (e.g., /da1/ vs. /bu4/) results in a value of 3. This additive framework generated a symmetric 8 × 8 RDM, with diagonal values (self-comparisons) set to 0 and off-diagonal values ranging from 1 to 3.

Tone-Weighted Model

To test the hypothesis that Tone carries higher perceptual salience in speech processing, this model assigns a doubled weight (2) to Tone changes, while maintaining unit weights (1) for Vowel and Consonant changes. Dissimilarity values are calculated as follows: A Tone change alone (e.g., /da1/ vs. /da4/) contributes a dissimilarity of 2. A combination of Tone with another feature (e.g., Tone + Vowel: /da1/ vs. /du4/) results in a summed value (2 + 1 = 3). Full feature changes (Tone + Vowel + Consonant) yield a maximum dissimilarity of 4 (2 + 1 + 1). This model’s RDM retains symmetry but amplifies dissimilarities involving Tone changes compared to the base model.

Vowel-Weighted Model

This model prioritizes Vowel changes with a weight of 2, hypothesizing that vowel identity dominates perceptual discrimination. Tone and Consonant changes retain unit weights (1). Key calculations included: A Vowel-only difference (e.g., /da1/ vs. /di1/) produces a dissimilarity of 2. Combinations involving Vowel changes (e.g., Vowel + Consonant: /da1/ vs. /bu1/) generate higher values (2 + 1 = 3). Triadic feature changes (Tone + Vowel + Consonant) reach a dissimilarity of 4 (1 + 2 + 1). The RDM structure emphasizes vowel-related distinctions while preserving additive feature contributions.

Consonant-Weighted Model

Mirroring the Vowel-Weighted Model, this framework assigns a weight of 2 to Consonant changes, reflecting a theoretical focus on consonantal salience. Tone and Vowel changes are weighed as 1. Dissimilarity computations included: A Consonant-only difference (e.g., /da1/ vs. /ba1/) is assigned a value of 2. Consonant-involving combinations (e.g., Consonant + Tone: /da1/ vs. /ba4/) yielded summed values (2 + 1 = 3). Full feature changes result in a maximum dissimilarity of 4 (1 + 1 + 2). This model’s RDM highlights dissimilarities driven by consonant alterations.

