##### Step 2: Calculating Neural RDM

Neural RDMs were computed based on ERP data, focusing on specific time windows (e.g., eMMN, lMMN, P3a). For each stimulus, the mean amplitude in the relevant time window was extracted. The neural dissimilarity between each pair of stimuli was quantified using either Euclidean distance or Pearson correlation. This process was repeated for each time window of interest, resulting in a series of neural RDMs.

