##### Step 3: Comparing Neural RDM with Theoretical Models

To assess how well neural responses align with theoretical models, we compute Spearman’s rank correlation between each neural RDM and the candidate theoretical RDMs. This comparison is performed separately for each time window (eMMN, lMMN, P3a). For group-level comparisons, we conduct the RSA separately for individuals with ASD and TD groups to examine potential differences in how speech features are neurally represented. We use permutation testing combined with cluster-based correction to control multiple comparisons and assess significant differences between groups.

These models assume that phonological features contribute additively to auditory dissimilarity, consistent with the view that early auditory encoding tracks separable acoustic dimensions (e.g., pitch, formant structure, place of articulation) without strong nonlinear interactions. The use of weighted models reflects the hypothesis that tone, vowel, or consonant cues may be differentially salient in perception—especially in tonal languages like Mandarin. While interactive or nonlinear RDMs could in principle be constructed (e.g., hierarchical cue interactions or phonological feature geometry), they require stronger theoretical constraints and larger datasets to validate. Thus, the current additive scheme balances theoretical interpretability, perceptual relevance, and statistical robustness. We employed RSA because it extends beyond univariate amplitude analyses by leveraging multivariate patterns of neural responses, allowing detection of distributed representational differences even when traditional ERP measures yield weak or non-significant effects. This approach is highly suitable for multi-feature paradigms, as it can capture subtle shifts in neural encoding across complex feature combinations and evaluate their alignment with theoretically derived perceptual models [80].

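### Feature salience is a claim about relative weight, but each weighted model is scored only by its own correlation with the neural RDM, which cannot show that one feature weighs more than the others

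*Protocol article*

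**What the plan says.** Section 2.3.4, Step 1, defines four model RDMs over the eight syllables. Of the Base Feature-Count model it says: "This baseline model assumes equal perceptual salience across all three features". The other three models each double one feature, with a relative hypothesis attached:

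- Tone: "To test the hypothesis that Tone carries higher perceptual salience in speech processing, this model assigns a doubled weight (2) to Tone changes".
- Vowel: "This model prioritizes Vowel changes with a weight of 2, hypothesizing that vowel identity dominates perceptual discrimination".
- Consonant: "this framework assigns a weight of 2 to Consonant changes, reflecting a theoretical focus on consonantal salience".

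Step 2 leaves the neural distance open: "The neural dissimilarity between each pair of stimuli was quantified using either Euclidean distance or Pearson correlation".

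Step 3 gives the fit statistic as Spearman's "rank correlation between each neural RDM and the candidate theoretical RDMs", computed separately for each time window and each group. The one inferential procedure named is permutation with cluster-based correction, for differences between ASD and TD. Step 3 describes no contrast between models, no partial correlation and no joint regression on the separate features. It gives no rule for when a salience hypothesis counts as supported.

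**The concern.** To say that tone is more salient is to say that tone weighs more than vowel and consonant. The natural comparator is equal weights, and the article supplies it as the Base model. A weighted model's own correlation with the neural RDM does not measure extra weight. Each weighted model is the Base model plus one further unit for one feature, so it correlates with any neural RDM that carries feature structure of almost any kind.

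Two readings are at risk. Within a group, a high tone-weighted fit could be reported as tone salience when all features count the same. Between groups, a lower tone-weighted fit in ASD could be read as bearing on the fourth key question in section 1.4, whether tone-related differences are the most pronounced. Yet an across-the-board weakening of feature coding would also lower that fit, and prediction P10 (section 3.2.2) expects reduced dissimilarity in all conditions.

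**Working it through.** **Inputs.** Eight syllables from three binary features (Table 3) give 8 × 7 / 2 = 28 pairs. The seven change types (T, V, C, TV, TC, VC, TVC) contribute 4 pairs each. Weights come from Step 1: Base 1/1/1, and 2 for the favoured feature in each weighted model.

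**Reproducing the article's figures.** Base takes values 1 (12 pairs), 2 (12) and 3 (4), which agrees with "This additive framework generated a symmetric 8 × 8 RDM, with diagonal values (self-comparisons) set to 0 and off-diagonal values ranging from 1 to 3". Tone-weighted takes 1 (V, C: 8 pairs), 2 (T, VC: 8), 3 (TV, TC: 8) and 4 (TVC: 4), so its maximum is the stated 4.

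**Overlap of the models.** Spearman's rho is the Pearson correlation of midranks; the mean rank is 14.5.

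- Base deviations from the mean rank: −8, 4, 12. Sum of squares 12×64 + 12×16 + 4×144 = 1536.
- Tone-weighted deviations: −10, −2, 6, 12. Sum of squares 8×100 + 8×4 + 8×36 + 4×144 = 1696.
- Base with tone-weighted: cross-product 640 (V, C) + 64 (T) − 32 (VC) + 192 (TV, TC) + 576 (TVC) = 1440. rho = 1440 / √(1536 × 1696) = **0.892**. By symmetry the vowel and consonant models give the same value.
- Tone-weighted with vowel-weighted: 80 (T) + 80 (V) + 400 (C) + 144 (TV) − 48 (TC) − 48 (VC) + 576 (TVC) = 1184. rho = 1184 / 1696 = **0.698**.

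**Noiseless neural RDMs with known weights.**

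| True weights | Base | Tone | Vowel | Consonant |
|---|---|---|---|---|
| All equal | 1.00 | 0.892 | 0.892 | 0.892 |
| Tone doubled | 0.892 | 1.00 | 0.698 | 0.698 |
| Tone zero | 0.732 | 0.358 | 0.809 | 0.809 |

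Under equal weights, permuting the stimulus labels in all 8! = 40,320 ways gives p = 0.0012 for the tone model. The vowel and consonant models give the same p, so three mutually exclusive dominance hypotheses would pass together.

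**Tone-zero row.** The no-tone RDM takes 0 (T), 1 (V, C, TV, TC) and 2 (VC, TVC), with rank deviations −12, −2, 10 and sum of squares 1440. The cross-product with the tone model is 96 + 160 − 96 − 80 + 480 = 560. rho = 560 / √(1440 × 1696) = 0.358.

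**Group comparison, simulated.** Assumptions: 30 children per group, 10 pattern dimensions, unit feature separation, 5% level, and all squared feature distances halved in ASD so that relative weights are unchanged. The test of tone-weighted fit between groups rejects in about 12% of runs at noise SD 1.0 and about 60% at SD 0.5; repeat runs gave 12–14% and 61–64%. A direct contrast of the tone weight with the mean of the vowel and consonant weights rejects in about 5%.

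**The case against.** The article never tests a single fit against zero and never writes down a null for one, so any rejection rate for such a test describes an analysis it does not announce. It calls the equal-weight model a baseline and the RDMs candidates, which suggests that fits will be compared. Ranking the four noiseless fits separates the three scenarios in the table correctly. None of P1–P12 names a tone-, vowel- or consonant-weighted model (P5, P6 and P11 name others), and the study is described as exploratory. How candidate models are contrasted is often left to a fuller analysis plan.

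Much of this stands, and it limits the point. A reader might infer that the plan would declare tone salient even if tone were not coded at all. The documents do not support that. With tone at zero the fit is positive (0.358), but it is the lowest of the four, and exact label permutation without noise gives p = 0.079. Whether it reaches significance depends on a test that the article does not state. With 32 assumed channels, a subject-level test against zero rejected in 54–100% of runs and label permutation in 22–32%. With a single mean amplitude per stimulus the figures were 8–58% and 1–9%.

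The objection does not remove the core. Step 3 names a statistic for a named hypothesis, and that statistic cannot test it. Informal ranking is not a calibrated substitute: under equal weights at noise SD 1.0–1.5 the tone model still ranked first in about 24–27% of simulated runs. The between-group test that Step 3 does state has the same weakness, whatever null is chosen for a single fit.

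**Conclusion.** The point holds as a mismatch between hypothesis and statistic. That equal weights fit all three weighted models at 0.89 is exact arithmetic on the article's own definitions and needs no noise assumption. A high fit of one weighted model is therefore not evidence that its feature is more salient.

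The group-level fault is real, but its size depends on assumptions. Rejection of about 12% at noise SD 1.0 and about 60% at SD 0.5, against about 5% for the direct contrast, rests on 10 dimensions, those noise levels and a halving of squared distances; none of these is in the article. The tone-zero case is a possibility that turns on the unstated test, not an expected result. Because no listed prediction uses the weighted models, what is affected is the salience interpretation in section 2.3.4 and any answer to the fourth key question drawn from it, not the predictions P1–P12.

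**What to change.** In Step 3, base salience claims on one direct contrast per child and time window, in either of two forms:

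1. **Paired fit difference.** Tone-weighted fit minus the mean of the vowel- and consonant-weighted fits. This keeps all four models. Under equal weights the three weighted models are exchangeable, so its expected value is zero.
2. **Regression contrast.** Regress the 28 squared Euclidean distances on the three single-feature RDMs plus an intercept, and take the tone weight minus the mean of the vowel and consonant weights. Each feature differs in 16 of 28 pairs and any two differ together in 8, so the predictors correlate only (8/28 − (16/28)²) / ((16/28)(12/28)) = −0.17. This form requires settling on Euclidean distance, which Step 2 leaves open.

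Test the contrast within each group and, by permuting group labels, between ASD and TD. Do the same for vowel and consonant. Add a sentence saying that a positive fit of one weighted model is not in itself evidence of salience.

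The cost is one paragraph and a few lines of code on the same RDMs. The price is lower apparent success: with tone truly doubled, power of the contrast is about 99% at noise SD 0.5 and about 45% at SD 1.0, under the same assumed 10 dimensions and 30 children per group.

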##### Step 2: Calculating Neural RDM

Neural RDMs were computed based on ERP data, focusing on specific time windows (e.g., eMMN, lMMN, P3a). For each stimulus, the mean amplitude in the relevant time window was extracted. The neural dissimilarity between each pair of stimuli was quantified using either Euclidean distance or Pearson correlation. This process was repeated for each time window of interest, resulting in a series of neural RDMs.

##### Step 3: Comparing Neural RDM with Theoretical Models

To assess how well neural responses align with theoretical models, we compute Spearman’s rank correlation between each neural RDM and the candidate theoretical RDMs. This comparison is performed separately for each time window (eMMN, lMMN, P3a). For group-level comparisons, we conduct the RSA separately for individuals with ASD and TD groups to examine potential differences in how speech features are neurally represented. We use permutation testing combined with cluster-based correction to control multiple comparisons and assess significant differences between groups.

These models assume that phonological features contribute additively to auditory dissimilarity, consistent with the view that early auditory encoding tracks separable acoustic dimensions (e.g., pitch, formant structure, place of articulation) without strong nonlinear interactions. The use of weighted models reflects the hypothesis that tone, vowel, or consonant cues may be differentially salient in perception—especially in tonal languages like Mandarin. While interactive or nonlinear RDMs could in principle be constructed (e.g., hierarchical cue interactions or phonological feature geometry), they require stronger theoretical constraints and larger datasets to validate. Thus, the current additive scheme balances theoretical interpretability, perceptual relevance, and statistical robustness. We employed RSA because it extends beyond univariate amplitude analyses by leveraging multivariate patterns of neural responses, allowing detection of distributed representational differences even when traditional ERP measures yield weak or non-significant effects. This approach is highly suitable for multi-feature paradigms, as it can capture subtle shifts in neural encoding across complex feature combinations and evaluate their alignment with theoretically derived perceptual models [80].

## 3. Predictions Based on Theory- and Data- Driven Perspectives

To guide our analysis and interpretation, we present two complementary sets of predictions derived from distinct sources: (1) a theory-driven framework integrating EPF, WCC, and NCH; and (2) a data-driven framework grounded in the empirical MMN literature. This approach ensures that our expectations are both conceptually motivated and empirically constrained. Predictions are formulated for two levels of analysis: temporal principal component analysis (t-PCA) and representational similarity analysis (RSA). t-PCA will be used to decompose the ERP signal into temporally distinct components (e.g., early MMN, late MMN), from which amplitude and latency estimates are derived. RSA will assess the structure of neural representations across conditions.

### 3.1. Theory-Driven Predictions (Based on EPF, WCC, and NCH Frameworks)

Here, we make some predictions from the tentative local vs. global processing framework (Table 1), which integrates the core tenets of EPF (enhanced local processing), WCC (impaired global integration), and NCH (escalating deficits with complexity). We focus on the eMMN and lMMN components and treat this framework as provisional and testable, acknowledging that the local/global distinction may not fully capture the neurophysiological reality of speech perception.

#### 3.1.1. t-PCA-Level Predictions (P)

P1 (Component Variance): The proportion of variance explained by temporally decomposed MMN components (eMMN, lMMN) will be lower in the ASD group for multi-feature deviants (V + T, C + T, C + V + T), reflecting less structured neural responses under high integrative demand.

P2 (Factor Scores): Factor scores for MMN-related components will be significantly reduced in the ASD group, particularly for tone-involving conditions (T, V + T, C + T, C + V + T), consistent with a global integration deficit.

P3 (Temporal Dynamics): The ASD group will show a delayed peak in late MMN (lMMN) components across all conditions, with the greatest delay observed for triple-feature deviants, supporting NCH’s prediction of cascading processing delays.

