#### 2.3.3. Temporal Principal Component Analysis

Given the use of a multi-feature oddball paradigm in the present study, the ERP components elicited by different deviant types are likely to overlap temporally, making it challenging to isolate the MMN using conventional fixed-window analysis. Prior studies have successfully applied temporal principal component analysis (t-PCA) to decompose overlapping ERP components and better isolate specific responses such as the MMN in oddball paradigms [73,74]. To address this issue, this study will employ t-PCA, a data-driven approach to decompose the ERP signal into latent temporal components. t-PCA enables the extraction of principal components that account for the majority of variance in the time domain, and through rotation and back-projection, allows psychologically meaningful components to be reconstructed in ERP space [75]. Compared to traditional averaging methods, t-PCA offers improved component separation, higher signal-to-noise ratio, and greater sensitivity in detecting condition-specific effects—advantages particularly critical for paradigms involving multi-dimensional speech feature processing (see Figure 2).

To extract multiple ERP components elicited by the multi-feature oddball paradigm, including early mismatch negativity (eMMN), and late mismatch negativity (lMMN), we decompose the time-domain covariance structure of the ERP data and identifies latent temporal components that account for the greatest proportion of variance in the signal.

t-PCA is applied across all conditions and participants, using the covariance matrix and Promax oblique rotation to enhance interpretability and allow for potential correlations among components. Component selection was guided by three criteria: (1) latency and temporal distribution of the component; (2) polarity and waveform characteristics; and (3) topographic distribution across the scalp. Based on previous literature and the typical temporal-spatial profiles of the target components, the following components are identified:eMMN: Early mismatch negativity (~100–200 ms; Fz, FCz, Cz)lMMN: Late mismatch negativity (~200–300 ms; Fz, FCz, Cz)P3a: Fronto-central positivity (~250–350 ms; Fz, FCz, Cz)

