## 4. Expected Results

Recruitment began during the third quarter of 2024 and is expected to run for 6 to 9 months, with final data collection anticipated within the first quarter of 2025. Data analysis and interpretation should be completed by the final quarter of 2025.

Upon completion of this study, the expected results will (1) identify neural response patterns derived from temporally decomposed components (eMMN, lMMN) that differentiate ASD and TD groups, particularly highlighting reduced variance explanation and weakened factor scores in the ASD group; (2) clarify differences in single-feature discrimination and multi-feature integration between the two groups, with specific emphasis on diminished sensitivity to increasing feature complexity in ASD, with the most pronounced group differences observed in dual- and triple-feature condition; (3) evaluate the fit of theoretical models of speech integration using Representational Similarity Analysis (RSA); and (4) reveal temporal dynamics of neural integration by examining how the similarity between neural RDMs and theoretical models evolves across the MMN time window. We expect that neural representational structures in the TD group will align more closely with an “Integrated Features” model, while the ASD group may show a stronger fit with a “Segmental-Only” model, supporting a local processing bias. We also expect that group differences in representational structure will become more pronounced in the late MMN (lMMN) period, reflecting delayed or disrupted higher-order integration in ASD. These results will provide a comprehensive, multi-level understanding of how children with ASD process and integrate speech features in a tonal language context.

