Finally, the relatively small sample size and multilevel analytical approach limit our ability to model individual differences comprehensively. Although we aim to collect data on ASD symptom severity (GARS-2), age, and gender, these variables could not be fully included as covariates in formal models due to power constraints. They can be considered in exploratory analyses. Notably, the sample is gender-imbalanced (28 males, 2 females), reflecting the higher male prevalence in ASD but potentially limiting generalizability, especially given known sex differences in auditory processing and ASD phenotypes. A central challenge in studying auditory and speech processing in ASD is the substantial heterogeneity within the population. Children with ASD exhibit a wide range of language outcomes, from minimally verbal to age-appropriate or even advanced language skills. Similarly, auditory hypersensitivity (e.g., distress to loud sounds) is a common sensory feature in ASD, but not universal. Some individuals may show a preference for nonspeech sounds over speech and others may not. This variability is not merely noise to be controlled for; it may be central to understanding the diverse profiles of speech perception. Future studies with larger, demographically balanced samples and integrated behavioral assessments will be essential to validate group/subgroup differences as well as individual differences and extend these findings.

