**Figure 2 brainsci-15-00905-f002:**
[figure not shown]
t-PCA pipeline for ERP data in the multi-feature oddball paradigm. (**A**) Data Matrix Setup. The matrix is labeled by Conditions × Time Points × Electrodes, representing trials collected across different stimulus types. (**B**) Covariance Matrix. Covariance matrix is essentially a mathematical tool that helps capture how the data varies over time and across different participants and conditions. (**C**) Principal component analysis. After we obtain the covariance matrix, the next step for t-PCA is to perform eigenvalue decomposition of the covariance matrix to extract the Principal Components from it. These principal components can be seen as new variables extracted from the original EEG signal, which reflect the change pattern of the maximum variance in the data. (**D**) Rotation. The principal components are adjusted using rotation techniques, such as Promax rotation, to improve interpretation. The purpose of the rotation is to make the interpretation between the individual principal components clearer and allow them to have correlations that are more in line with the actual electrical activity of the brain. (**E**) Component identification. By rotating the components, we can begin to identify the individual ERP components that make sense, such as eMMN, lMMN, and P3a. (**F**) Back-Projection and Reconstructed ERP. Components being projected back to ERP space. We multiply the loading matrix of each principal component with the factor scores under each condition to obtain the reconstructed waveform. The reconstructed waveforms contain the specific variation structure of each principal component in the ERP signal, and these waveforms can be interpreted in µV units, like traditional ERP waveforms. (**G**) Amplitude Extraction and Statistical Comparison. This final panel shows mean amplitude extraction from the reconstructed ERP data and reflects statistical testing (e.g., *t*-tests, ANOVA) to assess group differences or condition effects.

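### P1 reads a lower share of variance on the MMN components as less structured neural responses in ASD, but that share also depends on between-child spread and residual noise, so the MMN does not fix its direction

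*Protocol article*

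**What the plan says.** Section 3.1.1 of the protocol article predicts: "P1 (Component Variance): The proportion of variance explained by temporally decomposed MMN components (eMMN, lMMN) will be lower in the ASD group" for the V + T, C + T and C + V + T deviants, and interprets the lower value as "reflecting less structured neural responses under high integrative demand". Section 4 carries the prediction into the first of its four expected results, "particularly highlighting reduced variance explanation and weakened factor scores in the ASD group".

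The quantity comes from the decomposition in section 2.3.3: "t-PCA is applied across all conditions and participants, using the covariance matrix and Promax oblique rotation to enhance interpretability". The Figure 2 caption says that the covariance matrix "helps capture how the data varies over time and across different participants and conditions", and it lists electrodes as a dimension of the data matrix. The input is one averaged waveform per condition (section 2.3.2). Section 6 states: "A central challenge in studying auditory and speech processing in ASD is the substantial heterogeneity within the population".

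**The concern.** A proportion of variance explained describes a set of waveforms. It is not a property of one child's response. When the rows of the matrix are children, conditions and electrodes, the variance includes how much the children differ from one another, how large the other components are, and how much noise is left in each average. P1 attributes a change in this ratio to one cause, reduced organisation under integrative load, although several other causes move it.

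If P1 is kept, noisier ASD averages could appear to confirm it while the MMN is intact. A sufficiently heterogeneous ASD group could appear to refute it while the MMN is truly reduced. Neither result would say anything about integration, yet section 4 gives the measure a place among the expected findings.

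**Working it through.** P1 states no number, so there is no figure to reproduce. The check has an algebraic part and a simulation.

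**Inputs from the protocol article**
- Groups of 30 and 30 (section 2.1.2).
- Deviant trials: 980 / 7 = 140 per type before rejection (section 2.2.2).
- 32 channels, 250 Hz after downsampling, average reference, ±75 µV rejection (section 2.3.1).
- Epoch from -100 to 700 ms (section 2.3.2).
- Covariance t-PCA with Promax (section 2.3.3).

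**Inputs assumed.** The article gives no MMN mean, between-child SD or noise level. The TD reference was mean 2 µV, SD 1 µV, noise SD 1.5 µV. For ASD the mean was varied from -50% to +25%, the SD from 1 to 2.5 times, and the noise from 1 to 1.5 times. Noise in an average scales with 1/√n, so 1.5 times the noise corresponds to 140 / 1.5² ≈ 62 retained trials instead of 140.

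**Algebra.** Let μ be the mean component amplitude, SD its between-child SD, and R all other variance including noise.

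With electrodes among the rows, as in the Figure 2 caption, share = (μ² + SD²) / (μ² + SD² + R):

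| Case | μ | SD | R | Share |
|---|---|---|---|---|
| Reference | 2 | 1 | 5 | 5/10 = 0.50 |
| Same MMN, more spread | 2 | 2 | 5 | 8/13 = 0.62 |
| Same MMN, R doubled | 2 | 1 | 10 | 5/15 = 0.33 |
| MMN halved | 1 | 1 | 5 | 2/7 = 0.29 |
| MMN halved, SD doubled | 1 | 2 | 5 | 5/10 = 0.50 |
| MMN halved, SD × 2.5 | 1 | 2.5 | 5 | 7.25/12.25 = 0.59 |
| MMN enhanced, R doubled | 2.5 | 1 | 10 | 7.25/17.25 = 0.42 |

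With participants alone as rows at one site, share = SD² / (SD² + R) and μ drops out. The reference is 1/6 = 0.167; it becomes 4/9 = 0.444 at SD 2 and 1/11 = 0.091 at R = 10.

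**Simulation.** Covariance PCA with Promax and six factors, eight stimuli, 12 replicates per scenario, eMMN + lMMN share for one deviant, from the joint decomposition. The TD share was about 0.19 throughout. With identical groups the difference was -0.006, which indicates the simulation error.

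| ASD scenario | ASD minus TD |
|---|---|
| MMN unchanged, SD × 1.5 | +0.011 |
| MMN unchanged, SD × 2 | +0.052 |
| MMN unchanged, noise × 1.25 | -0.018 |
| MMN unchanged, noise × 1.5 | -0.035 |
| MMN -25% alone | -0.026 |
| MMN -25%, SD × 1.5 | -0.015 |
| MMN -25%, SD × 2 | +0.027 |
| MMN -50% alone | -0.050 |
| MMN -50%, SD × 2 | -0.003 |
| MMN -50%, SD × 2.5 | +0.046 |
| MMN +25%, noise × 1.5 | -0.019 |

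Separate decompositions by group gave the same signs.

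**Share computed per child and then averaged.** Taking a²/(a² + R) for each child with a ~ N(μ, SD²): the reference (μ = 2, SD = 1, R = 5) is 0.419. Doubling SD gives 0.442, a much smaller shift than in the pooled version. Doubling R gives 0.288. Halving μ alone gives 0.223, and halving μ with SD 2.5 gives 0.404, which nearly hides the loss.

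**The case against.** **P1 may mean a share per child.** Section 3.1.1 does not say that the share is pooled over children, and an article may leave the formula to a fuller plan. A per-child share is indeed less sensitive to heterogeneity, and this stands. It still falls with noise, so the interpretation is not rescued.

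**The share does follow the MMN.** A reader might infer that it moves regardless of the MMN. The documents do not support that. With electrodes in the matrix, a lower mean alone lowers the share (-0.026 at -25%, -0.050 at -50%). What fails is the inference from the share back to the MMN or to integration.

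**The plan can produce the shares.** A reader might infer that one joint decomposition yields a single share per component and cannot serve P1. Section 2.3.3 describes factor scores for each condition and participant, so shares by group and deviant type can be formed from it.

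**The drivers are not established.** A reader might infer that ASD averages will be noisier or that heterogeneity will reverse the result. Section 6 describes heterogeneity in language, sensitivity and sound preference, not in MMN amplitude. Section 2.1.2 excludes children with excessive head movement, and section 2.3.1 applies PREP, ICA and amplitude rejection. Neither direction of bias can be predicted. However, the article states no step that would equalise retained trials or separate these influences from structure.

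**The stakes are limited.** P1 is one of twelve predictions. Section 2.3.3 and Figure 2 panel G place testing on reconstructed mean amplitudes, and sections 3.1 and 6 call the framework provisional and the findings preliminary. This limits the damage, but an exploratory label does not change what an index measures.

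**Conclusion.** The point holds as a fault in the interpretation of P1 and of expected result (1). The share reflects mean amplitude, between-child variance, other components and noise together, so a lower or higher value in ASD does not identify a change in structure or integration.

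The directions follow from the algebra. The sizes rest on assumed amplitudes, SDs and noise. Under those values, 1.25 to 1.5 times the noise lowered a share of about 0.19 by 0.018 to 0.035 with an intact MMN, comparable to a true 25% loss (0.026). Heterogeneity needs to be large to mislead: an ASD SD of about 2 to 2.5 times the TD SD was required to mask or reverse a 25–50% loss, and the effect of SD × 1.5 alone was close to simulation error. The change is worth making but does not threaten the study's main comparisons.

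**What to change.** - Withdraw P1, and the phrase on reduced variance explanation in section 4, as evidence about structure or integration.
- Report variance explained only as a description of the joint decomposition.
- Rest the t-PCA group inference on component amplitudes or factor scores and on latencies, as P2, P3, P7 and P8 already do.
- If a structure index is wanted, use one formed within each child from the existing epochs. An example is the correlation between the odd-trial and even-trial component waveforms across time and electrodes, with equal trial counts per child and condition. Report it beside each child's residual noise, which still affects it.
- Do not substitute a split-half reliability coefficient of amplitudes computed across children. That coefficient is SD² / (SD² + half-test noise variance). With both terms at 1 it is 0.50; it falls to 1/(1 + 1.69) = 0.37 at 1.3 times the noise and rises to 4/5 = 0.80 at SD 2, so it has the same fault.

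The cost is two wording changes and the loss of one exploratory prediction. The optional index adds one computation and discards some trials to equalise counts.
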